**Figure 4 F4:**
[figure not shown]
Trial flow chart for the participants. ASI-R, the Appearance Schemas Inventory-revised; BR, breast reconstruction; CRF, clinical report form; EQ5D, EuroQoL-5 dimensions; HADS, Hospital Anxiety and Depression Scale; MBRSQ, the Multidimensional Body-Self Relation Questionnaire; PEGASUS, Patients’ Expectations and Goals of reconstruction. Assisting Shared Understanding of Surgery; SWAT, study within a trial; t, timepoint.

### Health economic analysis

A within-trial economic evaluation will be performed 36 months post allocation. The primary economic analysis will be a cost-effectiveness analysis presenting incremental cost-effectiveness ratios (ICERs). Effects will be expressed in terms of quality-adjusted life years, where the health-related quality of life will be assessed based on EQ-5D-3L using the UK Dolan tariff as well as a Swedish population-based tariff.^48 49^ A societal perspective will be adopted that includes healthcare costs and broader societal economic costs from sick leave based on the human capital approach. The healthcare costs will be based on inpatient, outpatient and primary care resource use and be collected from the controller of our departments (actual costs for the care given excluding any costs driven by the study protocols) and from Vega, the healthcare use database in Region Västra Götaland (VGR). Information on sick leave will be collected from the Swedish Social Insurance Agency (*Försäkringskassan* (https://www.forsakringskassan.se/english)) and information on the average income in different age groups from Statistics Sweden (*Statistikmyndigheten*, SCB (https://www.scb.se/en/)). ICERs and incremental net benefit (monetary/health) statistics will be assessed to compare the two interventions. The uncertainty will be assessed by non-parametric bootstrapping and visualised by means of cost-effectiveness planes and cost-effectiveness acceptability curves.

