**Methods and analysis:**

The study design partially randomised patient preference trial might be a way to overcome the aforementioned challenges. In the present study, patients who consent to randomisation will be randomised to implant-based and autologous breast reconstruction, whereas patients with strong preferences will be able to choose the method. The study is designed as a superiority trial based on the patient-reported questionnaire BREAST-Q and 124 participants will be randomised. In the preference cohort, patients will be included until 62 participants have selected the least popular alternative. Follow-up will be 60 months. Embedded qualitative studies and within-trial economic evaluation will be performed. The primary outcome is patient-reported breast-specific quality of life/satisfaction, and the secondary outcomes are complications, factors affecting satisfaction and cost-effectiveness.

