## Introduction

### Background and rationale

 Breast reconstruction is an integral part of modern breast cancer treatment.^1 2^ Nevertheless, evidence for the effectiveness of breast reconstruction methods is lacking with respect to increasing quality of life and achieving high patient satisfaction, with a low complication rate and societal economic costs. The low evidence is reflected in the varying guidelines for breast reconstruction and unequal access to different methods that have been seen in a European study,^3^ as well as in a report published by the Swedish Breast Cancer Association.^4^ Techniques for breast reconstruction can roughly be divided into two categories: *autologous* and *implant-based* techniques. Three systematic reviews^5^,^7^ have concluded that patients seem to have a higher breast-related quality of life when reconstructed with autologous techniques compared with implant-based techniques. However, most of the included studies were retrospective, non-randomised, did not correct for other factors that might affect satisfaction, and had a short follow-up. Moreover, few high-quality studies compare long-term cost-effectiveness^8^ and the long-term need for revisions, corrections, and donor-site consequences. All of these factors are essential to create evidence-based guidelines, prioritise the usage of healthcare resources and to give the patients information on which they can base decisions of breast reconstruction. There are no ongoing trials registered in ClinicalTrials.gov comparing different categories of breast reconstruction technique head to head (https://clinicaltrials.gov/search?cond=breastreconstruction (search performed 22 July 2023)).

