### Research hypotheses

It is hypothesised that

patients are more satisfied with the reconstructed breast/s when an autologous deep inferior epigastric perforator (DIEP) flap is performed.although a ‘simpler procedure’, implant-based reconstruction entails a higher total number of operations and revisions long-term, compared with autologous DIEP-flap.although a procedure that is more costly for the healthcare system when it is performed, an autologous DIEP-flap is more cost-effective for society in the long-term perspective, due to the long-term effects and consequences of implants.

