### Retention

Any trial participant lost to follow-up will be contacted to complete the 3, 12, 36 and 60 months follow-up. The trialists will make every reasonable effort to follow participants for the entire study period. If available, a reason for withdrawal will be documented.

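### The only stated economic evaluation is at 36 months, although the cost-effectiveness hypothesis is long-term and follow-up runs to 60 months

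*Protocol article*

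**What the plan says.** Three parts of the protocol article bear on the point.

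- **Research hypotheses.** The third hypothesis concedes that the flap is expensive at first ("although a procedure that is more costly for the healthcare system when it is performed") and then states that "an autologous DIEP-flap is more cost-effective for society in the long-term perspective, due to the long-term effects and consequences of implants". The second hypothesis points the same way: "implant-based reconstruction entails a higher total number of operations and revisions long-term, compared with autologous DIEP-flap". Background and rationale names the same evidence gap: "few high-quality studies compare long-term cost-effectiveness".
- **Length of follow-up.** The abstract states: "Follow-up will be 60 months". The Retention section confirms a last contact at that time: "Any trial participant lost to follow-up will be contacted to complete the 3, 12, 36 and 60 months follow-up".
- **Health economic analysis.** "A within-trial economic evaluation will be performed 36 months post allocation". This section specifies a cost-effectiveness analysis from a societal perspective. QALYs come from EQ-5D-3L, healthcare costs from the department controller and the regional healthcare-use database, and sick leave from the Social Insurance Agency. It describes no second evaluation at 60 months and no projection beyond 36 months, and it does not say why 36 months was chosen.

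**The concern.** The hypothesis describes a trade-off over time: a higher cost for the flap at surgery, offset later by what implants go on to require. A test of such a claim depends on its horizon. An early cut counts the whole initial cost difference and only part of any later offset. The evaluation stops two years before the trial's own last contact, so the data closest to the long-term question have no stated economic use.

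This matters because the Significance section expects the results to inform guidelines and the allocation of healthcare budgets. An unfavourable or inconclusive 36-month result could be read as evidence against a long-term claim that it addresses only in part.

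**Working it through.** The plan gives no numerical figure for the economic evaluation, so there is nothing to reproduce. The sample size rests on BREAST-Q and does not bear on the horizon. The check compares stated durations and then asks what they imply.

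**Inputs**
- Economic horizon: 36 months from allocation (Health economic analysis).
- Trial follow-up: 60 months (abstract), with contacts at 3, 12, 36 and 60 months (Retention).
- Assumption: both periods run from allocation. The article gives this origin for the 36 months but gives none for the 60.

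**Step 1: time left out**
- 60 − 36 = 24 months.
- 24 / 60 = 0.40, so the evaluation covers 36 / 60 = 0.60 of follow-up.

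**Step 2: what the cut does to the result**

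Let D be the extra cost of the flap at surgery, L(T) the extra later cost of implants up to month T, ΔQ(T) the QALY gain of the flap up to T, and λ the value placed on one QALY. The incremental net benefit, which the plan intends to report, is

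INB(T) = λ·ΔQ(T) − [D − L(T)].

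The difference between the two horizons is

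INB(60) − INB(36) = λ·[ΔQ(60) − ΔQ(36)] + [L(60) − L(36)].

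D cancels because it is counted in full at either horizon. If implants generate further net cost between months 36 and 60, and the flap does not lose QALYs relative to implants in that period, the right-hand side is positive and the 36-month result understates the flap's value. That is what the trial hypothesises. If those conditions fail, the sign can differ.

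**Step 3: can the difference be sized?**

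No. The article gives no costs, revision rates or EQ-5D differences over time. How far the 40% of time can lie from a share of cost is shown by three assumed patterns for the extra later cost of implants over 60 months:

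| Assumed rate of accrual | Share falling after month 36 |
|---|---|
| Falls linearly to zero at 60 months | (24/60)² = 0.16 |
| Constant | 24/60 = 0.40 |
| Rises linearly from zero | 1 − (36/60)² = 0.64 |

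None of these is an estimate for this trial. They show only that the same 24 months could hold much less or much more than 40% of the later difference.

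**The case against.** The best defence is that this is a design choice in a condensed article. A later update or an extrapolation is not excluded, and a health economic plan that is not shown may contain one. The hypothesis does not define long-term as beyond 36 months. Costs that fall early are captured: the Implant-based breast reconstruction section puts the exchange of a temporary expander at about 3 months, and early complications, corrections and sick leave also fall within the window. The section on considerations regarding the health economic analysis criticises modelling in earlier studies, which may explain why no projection is planned.

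Part of this stands. The article does not forbid a later analysis, and the early implant costs are counted. But the article fixes the horizon itself, so this is not a detail left to another document. A dislike of modelling explains the absence of extrapolation. It does not explain leaving out months that will be observed.

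A reader might infer more than the documents support:

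- **That the ratio is biased against the flap.** This direction follows only if the trial's own hypothesis about late implant costs is true, and no data in the article establish it.
- **That 40% of the cost or QALY difference is missed.** The 40% is calendar time. If revisions come early, less is missed.
- **That waiting for surgery shortens the flap's observed period further.** The section on risks gives theatre throughput, not waiting times, and says capacity can expand. Allocation is also a normal time origin for an intention-to-treat comparison.
- **That the hypothesis cannot be answered.** A 36-month analysis does address it, over a limited horizon.

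**Conclusion.** The point holds as a mismatch between hypothesis and horizon. The only economic evaluation the article states uses 36 of 60 follow-up months to test a claim about long-term consequences, and no reason is given. The omitted period is 24 months, or 40% of the time if both periods run from allocation. The effect on the cost-effectiveness ratio is of unknown size. Its direction, understating the flap's long-term value, is conditional on implant costs accruing late.

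The primary outcome, the sample size and the randomised comparison are unaffected. The change is worth making because it is cheap and answers the trial's own question better. The present plan would still produce a valid result for 36 months.

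**What to change.** Prespecify a within-trial cost-effectiveness analysis at 60 months and name it as the test of the long-term hypothesis. Keep the 36-month analysis as an earlier result, reported as applying to that horizon. Use the healthcare-cost and sick-leave sources already named, extended to 60 months, and EQ-5D-3L from the 60-month contact. The instrument schedule is in figure 4, which could not be seen here, so the authors should confirm that EQ-5D-3L is collected then and add it if it is not.

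If 36 months is to remain the only horizon, give the reason and limit the third hypothesis and its conclusions to 36 months.

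The cost is a further extract from the cost and sick-leave sources and, if needed, one short questionnaire at a contact already planned. No change to the sample size follows. The long-term economic result would come two years later (60 − 36 = 24 months), and more EQ-5D data would be missing by then. Sixty months also falls short of an implant's lifetime, so the change reduces the mismatch without removing it, and the report should say so.

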### Data collection and participant timeline

The participant timeline for the trial is shown in figure 4.

### Statistical methods

A detailed statistical analysis plan will be drafted early in the trial and finalised before primary outcome analysis. All analysis will be performed on an intention-to-treat basis and per-protocol analysis as sensitivity analysis. Descriptive data will be given as appropriate according to type of data and if it is skewed or not. This will also form the basis for statistical tests chosen to compare groups. Sensitivity analysis will be done were missing data in predictors will be handled by multiple imputation methods.^50^ Regression analysis preceded by collinearity check of potential predictors and performed to allow for correction for possible confounders. Residuals for each regression analysis will be checked for the assumptions of normal distribution and constant deviation along the predicted values. Subgroup analyses will be performed for the randomised and the preference cohort and for timing of reconstruction (immediate/delayed reconstruction) and for patients who unexpectedly will require radiotherapy. The statistical analysis will adhere to the Setting Intenartional Standards in Analysing Patient-Reported Outcomes and Quality of Life Endpoints in Cancer Clinical Trials (SISOQOL) framework.^51^ All tests will be two tailed and a p value of ≤0.05 will be considered to indicate a statistical significance.

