A PubMed search on breast AND reconstruction, limited to RCTs, yields 419 results (10.07.2023).^14^ One-hundred and nine of them are RCTs concerning some aspect of breast reconstruction. The majority compared surgical variation within the same category of breast reconstruction technique, for example, one versus two stages or mesh versus no mesh in implant-based breast reconstruction and preoperative imaging versus no preoperative imaging in autologous breast reconstruction. Only four studies compare different categories of breast reconstruction techniques head to head^15^,^18^ and they all illustrate the aforementioned challenges with RCTs in breast reconstruction. For example, in the RCT performed in our department, the Gothenburg Breast Reconstitution trial (GoBreast),^18 19^ preintervention dropouts rates after randomisation varied between 12.5% and 23% in different groups, due to either the patient’s or surgeon’s preferences.

The study design partially randomised patient preference trial (RPPT) is an approach to diminish the impact of patients’ preferences, facilitate recruitment, increase patient centricity, decrease the risk of excluding large patient groups and make the results more generalisable to the clinical population, when preference-sensitive interventions are compared.^20^ In an RPPT, patients with a clear preference are treated accordingly and patients without a distinct preference are randomised in the traditional way. The RPPT design enables a more efficient inclusion of participants, and a clinically more representative study population, while maintaining a high external and internal validity.^20^ GoBreast II will mark the first use of an RPPT design to evaluate breast reconstruction methods.

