### Study objectives

The main overall purpose of breast reconstruction is to increase the woman’s quality of life, both physically and psychosocially. Therefore, the primary objective/outcome is to compare the two methods regarding patient-reported breast-specific quality of life and satisfaction. These measures are also part of the core outcome set for breast reconstruction developed by patients and professionals.^21^

The secondary objectives are to compare the two methods regarding complications, unplanned operations, corrections, cost-effectiveness and factors that might affect the primary outcome. Other secondary objectives are to improve the evidence for trial decision-making in breast reconstruction to improve the methodological design and process of future studies by means of a study within a trial (SWAT).^22^

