### Criteria for discontinuing or modifying allocated interventions for a given trial participant

Trial participants have the right to withdraw from the study at any time without any consequence. Before the reconstruction, patients can change from the randomised cohort to the preference cohort should they change their wishes. Their data will then be analysed according to their change. If the patient regrets her choice of cohort after her reconstruction, she will be included in the analysis of her original cohort, but her change of preference will be noted.

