#### Secondary outcomes

All adverse events are classified according to the Clavien-Dindo Classification (CDC) of surgical complications and Comprehensive Complication Index (CCI) scores,^37^ as well as specific complications. CDC and CCI are currently being validated for breast reconstruction in our department. All participating surgeons will be given a list of study-specific definitions of *complications and corrections/revisions. Satisfaction with the donor-site* will be measured with BREAST-Q donor site domains, expectations with BREAST-Q expectations domain,^38 39^
*symptoms of depression and anxiety* with Hospital Anxiety and Depression Scale (HADS),^40 41^
*body image* with the Appearance Schemas Inventory-revised (ASI-R)^42^and the Multidimensional Body-Self Relation Questionnaire (MBSRQ),^43^
*generic quality of life* with EuroQoL-5 dimensions (EQ-5D-3L),^44^ and the *patient’s goals with the reconstruction* will be documented using PEGASUS.^20^

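### The blanket intention-to-treat rule also covers harms, so a complication in a woman who receives the other operation without having changed her own wishes is counted under the method she did not receive, or excluded per protocol

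*Protocol article*

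**What the plan says.** Statistical methods sets the analysis population in one sentence: "All analysis will be performed on an intention-to-treat basis and per-protocol analysis as sensitivity analysis". The sentence before it defers detail: "A detailed statistical analysis plan will be drafted early in the trial and finalised before primary outcome analysis". No analysis by operation received is named anywhere in the article.

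Harms are a comparison between methods. Study objectives states: "The secondary objectives are to compare the two methods regarding complications, unplanned operations, corrections, cost-effectiveness and factors that might affect the primary outcome". Research hypotheses predicts more operations and revisions in the long term with implants. Secondary outcomes gives the measures: "All adverse events are classified according to the Clavien-Dindo Classification (CDC) of surgical complications and Comprehensive Complication Index (CCI) scores", together with specific complications.

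One route by which allocation and treatment can part is handled, in the section on discontinuing or modifying allocated interventions: "Before the reconstruction, patients can change from the randomised cohort to the preference cohort should they change their wishes". It continues: "Their data will then be analysed according to their change". Trial design adds that women in the preference cohort are operated on with the method they prefer.

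The only related rate is in Background and rationale, about the department's earlier randomised trial: "preintervention dropouts rates after randomisation varied between 12.5% and 23% in different groups". The article attributes these losses to the preferences of patients or surgeons.

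**The concern.** Flap-specific and implant-specific complications can arise only from the operation performed. Take a woman allocated to a DIEP-flap who, by a decision made during surgery, receives an implant and later loses it. By intention-to-treat that loss counts against the DIEP-flap. A per-protocol analysis would normally leave her out. Neither analysis counts it against implants.

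A woman who is never operated on stays in the intention-to-treat denominator although she cannot have a surgical complication, which lowers the apparent risk of her arm.

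For a superiority question on BREAST-Q, dilution towards no difference is the cautious direction. For harms it is not, because it can make two methods with different risks look alike. The article hopes that its results could underpin a standard for what patients are told (Considerations regarding the included population and equipoise), so risks specific to each method matter.

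**Working it through.** **1. Which departures from allocation are covered**

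| Route | Rule in the article | Where a complication is counted |
|---|---|---|
| Woman changes her wishes before surgery | Analysed according to the change | With the method chosen and received |
| Surgeon decides on the other method | None beyond intention-to-treat / per-protocol | With the method not received, or excluded |
| Change during surgery | Same | Same |
| Preference patient ends up with the other method | Same | Same |
| Never operated on | Same | In the intention-to-treat denominator, no surgical event possible |

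The first row covers only changes that the woman herself makes. It also departs from strict intention-to-treat, because a randomised woman leaves her randomised group. The two sections therefore do not agree as written.

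**2. The plan's own figure**

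No harms figure is stated. The group size used below can be reproduced from Sample size (difference 10, SD 18, two-sided alpha 0.05, power 0.80, 20% dropout):

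- n = 2 × (1.96 + 0.84)² × 18² / 10² ≈ 51 per group.
- 51 × 1.2 = 61.2, rounded up to 62, as stated. Dividing by 0.8 instead gives 64.

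The same section gives at least 124 per arm when both cohorts are taken together.

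**3. Dilution from crossover**

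Assumptions, none of them in the article: true risks are 40% and 20%; a share c in each arm receives the other operation and stays in her allocated group; and her risk is that of the operation received.

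- Risk in one arm: (1 − c) × 40% + c × 20%.
- Risk in the other: (1 − c) × 20% + c × 40%.
- Difference: (1 − 2c) × 20 points. If only one arm crosses over: (1 − c) × 20 points.

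Power is from the two-proportion normal approximation for two-way crossover, with no loss to follow-up.

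| c | Women per 62 | Difference, two-way | Difference, one-way | Power, 62 per arm | Power, 124 per arm |
|---|---|---|---|---|---|
| 0 | 0 | 20.0 | 20.0 | 0.685 | 0.935 |
| 2% | 1.2 | 19.2 | 19.6 | 0.648 | 0.915 |
| 5% | 3.1 | 18.0 | 19.0 | 0.592 | 0.876 |
| 12.5% | 7.8 | 15.0 | 17.5 | 0.445 | 0.734 |
| 23% | 14.3 | 10.8 | 15.4 | 0.257 | 0.458 |

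The last two rows borrow the earlier trial's figures as an upper end. Those figures are dropout before intervention, not crossover.

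**4. Women not operated on**

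If a share u of each arm is never operated on, each risk is multiplied by (1 − u): 0.875 at 12.5% and 0.77 at 23%. Risks of 40% and 20% become 35% and 17.5%, or 30.8% and 15.4%. The absolute difference falls to 17.5 or 15.4 points. With equal loss in both arms the relative risk is unchanged.

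**The case against.** The strongest reply is that a safety population by operation received is a standard item of an analysis plan, which the article says will follow, and that a condensed article need not contain it. That would settle the matter if the article were silent. It is not: it states a rule for all analysis, and a later plan that counted harms by operation received would depart from it. The reply does lower the stakes, since the later plan may well correct this.

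A reader might infer that no switched woman's complication is ever counted with the operation that caused it. The article does not support that. Women who change their wishes before surgery are analysed according to the change, and this is the route that the preference design exists to handle. Per-protocol is also only a sensitivity analysis, so the event is not lost from the main analysis. Because specific complications are recorded, an implant loss remains identifiable as such; only the group it counts under is wrong.

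A reader might also take 12.5% to 23% as the crossover to expect here. Those figures are dropout in a conventionally randomised trial with other comparators, and they include patient preference, which this design largely diverts. Nor do the power figures at 62 per arm describe the whole trial, which has at least 124 per arm.

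Finally, intention-to-treat has a proper place for harms: the hypothesis on total operations in the long term is a question about a treatment strategy. Switches decided by surgeons are also selected, so a comparison by operation received should not simply replace it. This stands, and the remedy is to show both analyses.

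**Conclusion.** The point holds in a limited form. As written, the analysis rule counts complications under the wrong method, or excludes them per protocol, for women who receive the other operation for reasons other than their own change of wishes, and it keeps women who were never operated on in the denominator. How many women this concerns cannot be read from the article.

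On the assumed risks, the dilution is small if switches are rare (about 1 to 2 points of 20 at 2% to 5% two-way crossover). It is material only at the upper end (5 to 9 points at 12.5% to 23%). Misattribution of the individual event occurs at any rate. The separate mismatch between the reassignment rule and the intention-to-treat statement does not depend on any of these assumptions.

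**What to change.** - In Statistical methods, exempt harms from the blanket sentence. State that complications, reoperations and the CDC and CCI results are reported among operated women by the reconstruction actually received, alongside the intention-to-treat analysis.
- Keep intention-to-treat for BREAST-Q.
- Reconcile the section on discontinuing or modifying allocated interventions with the intention-to-treat statement. Say in which analyses a randomised woman who moves to the preference cohort counts under her new cohort, and in which under her allocation.
- Report per arm how many women received the other operation or none, with the reason, so that the size of the problem becomes visible.

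The cost is a few sentences in the protocol and the analysis plan, plus one further table. The article does not say outright that the operation performed is entered on the report form. It does provide for report forms, medical charts and registration of all implants, so new data collection should not be needed. There is a small downside: a comparison by operation received is not fully protected by randomisation, which is why both tables should be shown.
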